**Methods:**

This study will be a randomized, single-blind, and sham-controlled trial. The study will recruit 76 female patients diagnosed with SUI. They will be randomly allocated to two groups: acupuncture and sham acupuncture, in a 1:1 ratio. Each group of subjects will receive 10 min of acupuncture treatment at RN3 (Zhongji). Outcomes will be assessed at three time points: baseline, during intervention, and 10 min post-intervention, using pelvic floor muscle sEMG. The primary outcome will be the difference in mean amplitude (μV) of the sEMG recordings during the 10-second tonic contraction phase between the acupuncture and sham acupuncture groups. Secondary outcomes will include assessments of amplitude, variation coefficient, and relaxation time across the other phases of the sEMG evaluation. The trial will record adverse events related to the intervention.

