### Randomization

This study was designed as a randomized, sham-controlled trial. The randomization sequence was generated by an independent statistician using a computer-generated random number method (SPSS v26.0; IBM Corp., Armonk, NY, USA). Eligible patients were randomly allocated in a 1:1 ratio to either the acupuncture group or the SA group. The allocation sequence was prepared as sequentially numbered cards and sealed in opaque envelopes bearing corresponding identification numbers. After participants were formally enrolled and completed baseline assessments, an independent researcher not involved in the intervention or outcome assessment opened the envelopes sequentially according to the order of enrollment to obtain the allocation information. The group assignment was then promptly communicated to the acupuncturist responsible for delivering the intervention.

Throughout the study, investigators, outcome assessors, and data analysts will be blinded to group allocation. Strict allocation concealment procedures were implemented to minimize potential selection bias. The study design and reporting adhered to the CONSORT guidelines for randomized controlled trials.

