#### The secondary outcomes

(1) The mean amplitude in the prerest phase; (2) The variation coefficient in the prerest phase; (3) The maximum amplitude of five rapid contractions; (4) The relaxation time of five rapid contractions; (5) The variation coefficient in the 10-s tonic contraction phase; (6) The mean amplitude in the 60-s endurance contraction phase; (7) The variation coefficient in the 60-s endurance contraction phase; (8) The mean amplitude in the postrest phase; (9) The variation coefficient in the postrest phase.

Pelvic floor muscle sEMG will be measured using the MLD B4Plus (Biological feedback instrument, Mailande Medical Technology Co., Nanjing). Pelvic floor muscle sEMG will collect muscle movement potentials through a vaginal probe, providing insights into the strength, tone, and coordination of PFM (16, 17). The insertion of the vaginal probe will be conducted by a trained professional, with patients following the device's instructions to complete the assessment. The sEMG evaluation consists of five phases, assessing parameters such as amplitude, relaxation time, and the variation coefficient, which are indicative of clinical significance, as shown in Table 1. This assessment aids clinicians in gaining a comprehensive understanding of patients' PFM function.

**Table 1 T1:** Outcomes of pelvic floor muscle sEMG.

Domain	Meaning	Item	Unit
Outcomes			
sEMG in the prerest phase	measure the muscle tension of the PFMs in the resting status	mean amplitude‡	μV
		variation coefficient‡	
sEMG of five rapid contractions	measure the function of the fast-twitch fibers of the PFMs	maximum amplitude‡	μV
		relaxation time‡	s
sEMG in the 10-s tonic contraction phase	measure the function of the slow-twitch fibers of the PFMs	mean amplitude†	μV
		variation coefficient‡	
sEMG in the 60-s endurance contraction phase	measure the endurance of the slow-twitch fibers of the PFMs	mean amplitude‡	μV
		variation coefficient‡	
sEMG in the postrest phase	measure the recovery function of the PFMs	mean amplitude‡	μV
		variation coefficient‡	

†Primary outcome.

‡Secondary Outcomes.

sEMG, surface electromyography.

The sEMG measurements will be recorded at three time points: baseline (T_0_), during intervention (T_1_), and 10 min post-intervention (T_2_).

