### Statistical method

#### Sample size

The sample size was calculated using the PASS 15.0 software. The PFM function will be analyzed by a combination of parameters in the sEMG. According to a previous study [10], the contractility of the slow-twitch fibres in PFM function is the main urinary control factor. Therefore, the change in mean amplitude (μV) of the sEMG during the 10-s tonic contraction phase, which represents the contractility of the slow-twitch fibres, was selected for calculation. Based on pilot study data, the mean ± standard deviation (SD) is 4.1 ± 2.7 μV in the acupuncture group and 1.9 ± 1.6 μV in the SA group. 32 cases will be required in each group (α = 0.05, 1–β = 0.90). Taking into account the 15% dropout rate, 38 cases per group were required. Therefore, an optimal sample size of 76 cases will be required.

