#### Data analysis

All data will be analyzed using IBM SPSS Statistics (v26.0; IBM Corp, Armonk, NY, USA). The analysis will be conducted according to the intention-to-treat (ITT) principle, including all randomized participants. Safety analyses will be performed on the safety set, which includes all participants who received acupuncture. For both primary and secondary outcomes, missing data will be handled using generalized estimating equations (GEE), which provide valid statistical inference under the assumption of missing at random (MAR) without the need for explicit imputation. If the overall proportion of missing data exceeds 10%, sensitivity analyses will be performed to assess the robustness of the results to the missing data assumption. Missing data for safety outcomes will not be imputed.

Continuous variables will be presented as mean ± standard deviation (SD) if normally distributed, or as median (interquartile range, IQR) otherwise. Categorical variables will be summarized as frequencies and percentages. Baseline demographic and clinical characteristics will be compared using the chi-square test or Fisher's exact test for categorical variables, and independent-samples *t*-tests or Mann-Whitney U tests for continuous variables, as appropriate.

For repeated measurements obtained at three time points (T_0_, T_1_, and T_2_), GEE models will be used as the primary analytical approach to account for within-subject correlations. The models will include group, time, and group-by-time interaction terms, with an appropriate working correlation structure selected based on model fit and data characteristics. The group-by-time interaction will be examined first; if significant, simple effects analyses will be conducted, otherwise main effects will be interpreted. Multiple comparisons will be adjusted using the Bonferroni correction.

All adverse events (AEs) and serious adverse events (SAEs) will be listed. AEs will be classified as acupuncture-related or non-acupuncture-related events. The incidence of AEs will be summarized as the number and percentage of participants in each group and compared using Fisher's exact test. Given the exploratory nature of safety analyses, *P-*value will not be adjusted for multiple comparisons.

Effect sizes along with their 95% confidence intervals (CIs) will be reported. All statistical tests will be two-sided, and a *P* value <0.05 will be considered statistically significant.

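### When the group-by-time interaction is not significant, the plan falls back on main effects: the time effect contains no comparison with sham, and the group effect is a diluted second test that raises the false-positive rate from 5% to about 10%

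*Protocol article*

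**What the plan says.** The Data analysis section of the protocol article makes one repeated-measures model the main analysis: "For repeated measurements obtained at three time points (T_0_, T_1_, and T_2_), GEE models will be used as the primary analytical approach". On its terms it says: "The models will include group, time, and group-by-time interaction terms". T0 is therefore a response level, and no baseline covariate is named. The decision rule follows: "The group-by-time interaction will be examined first; if significant, simple effects analyses will be conducted, otherwise main effects will be interpreted". The section also promises a Bonferroni adjustment, without saying which tests form the family, and effect sizes with 95% confidence intervals.

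Other sections fix what these terms mean:

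- Randomization puts the opening of the envelope after baseline: "After participants were formally enrolled and completed baseline assessments".
- The outcomes section defines T0 as baseline, T1 as during needling and T2 as 10 minutes afterwards.
- The abstract (Methods) defines the primary outcome as a difference between the arms in mean amplitude of the 10-second tonic phase.
- Sample size works with the change in that amplitude and gives pilot values of "4.1 ± 2.7 μV in the acupuncture group and 1.9 ± 1.6 μV in the SA group".

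**The concern.** T0 precedes needling and the opening of the allocation, so it cannot carry a treatment effect. The between-arm difference in change from T0 is exactly what the group-by-time terms estimate. If those terms are not significant, the trial's question has had its test. The rule then turns to two other quantities.

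- **Time.** This main effect averages real and sham needling. Repeat testing, fatigue or expectation can move both arms, and the effect then becomes significant without any difference between them.
- **Group.** This main effect averages T0 with T1 and T2. It asks the between-arm question a second time, with a weaker contrast, after the first test has failed.

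The rule governs the primary outcome and, by the same wording, each of the nine secondary outcomes. The Discussion says that the T1 recording will show changes while patients receive acupuncture, and the Conclusion expects to show changes during acupuncture. A significant time effect after a null interaction would fit both sentences, yet it says nothing about acupuncture against sham.

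**Working it through.** **1. The plan's own figure.** Inputs from Sample size: difference 4.1 − 1.9 = 2.2 μV, two-sided α 0.05, power 0.90, dropout 15%. With SD 2.7 in both arms, n = 2 × (1.960 + 1.282)² × 2.7² / 2.2² = 31.7, so 32 per arm. Then 32/0.85 = 37.6, so 38 per arm and 76 in total. The plan's figure is reproduced, and its target is a between-arm difference in change of 2.2 μV. Using 2.7 in both arms is conservative, because the sham SD is 1.6.

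**2. What each term estimates,** if the 2.2 μV effect is present at both T1 and T2:

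- Group-by-time: 4.1 − 1.9 = 2.2 μV at each post-baseline time.
- Group main effect, equal weight on the three times: (0 + 2.2 + 2.2)/3 = 1.47 μV, two thirds of the effect.
- Time main effect: (4.1 + 1.9)/2 = 3.0 μV from T0. If acupuncture equals sham and both change by 1.9, it is still 1.9 μV.

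**3. Time main effect when acupuncture equals sham.** Reading the pilot figures as changes, the sham arm alone at 38 patients gives t = 1.9/(1.6/√38) = 7.3. The rule was also simulated: 6,000 trials per setting, 38 per arm, compound symmetry, 2-df tests for interaction and time. Assumptions that are not in the document: between-patient SD 3, 6 or 10 μV; SD of change 1.6 or 2.7 μV in both arms; a shift common to both arms of 0, 0.5, 1.0 or 1.9 μV.

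| Common shift | Time effect significant, change SD 1.6 | Change SD 2.7 |
|---|---|---|
| 0 | about 5% | about 5% |
| 0.5 μV | 79–80% | 35–36% |
| 1.0 μV | 100% | 91–92% |
| 1.9 μV | 100% | 100% |

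The rates are virtually the same when restricted to trials with a non-significant interaction.

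**4. Group main effect when acupuncture equals sham.** Taken alone it rejects in 4.6–5.2% of simulated trials, so it is a valid test. Under compound symmetry a patient's mean level and changes are independent. Interaction first and group second therefore gives 1 − 0.95² = 9.75%; the simulation gives 8.9–10.3%. Adding the time test with no shift gives 1 − 0.95³ = 14.3%; the simulation gives 13.3–14.4%.

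**5. Group main effect when there is an effect.** With between-patient SD b and change SD 2.7 (residual variance 2.7²/2 = 3.645), its standard error at 38 per arm is √[(2/38)(b² + 3.645/3)].

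- b = 3: 0.73, and 1.47/0.73 = 2.0
- b = 6: 1.40, and 1.47/1.40 = 1.05
- b = 10: 2.31, and 1.47/2.31 = 0.64

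The difference in change at one time has standard error 2.7 × √(2/38) = 0.62, and 2.2/0.62 = 3.55. Simulated power of the group main effect over both change SDs is 51–54%, 17–19% and 9–10% for b = 3, 6 and 10. For the interaction it is 96–100%.

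**6. Where the fallback is reached.** In about 95% of trials with no effect, and in about 0–4% of trials with the planned effect.

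**The case against.** Testing the interaction first and then the main effects is a familiar factorial convention. Here the interaction test is the right one in form, is done first and is well powered. Several stronger readings are tempting, and the document does not support them.

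- A reader might infer that the group main effect is no treatment effect at all. Randomisation makes the expected T0 difference zero, so it is a 5% test of a diluted effect.
- A reader might take the near-100% rate for time as a false-positive rate for acupuncture. It is not: the simulation put a real shift into both arms, and the test found it. It misleads only if read as acupuncture beating sham. The plan says that main effects will be interpreted, not that a time effect supports acupuncture, and the primary outcome is a between-arm difference.
- Simulation with uncorrected robust Wald tests gives 11.4–11.6% for interaction or group. Part of that is small-sample inflation: the interaction test alone rejects in 6.2–6.4%. With small-sample corrected tests the same rule gives 9.8–10.1%. The share due to the fallback is the rise from 5% to about 10%.
- Reaching the fallback in about 95% of null trials follows from any 5% test and is not itself a defect.

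All of this stands and limits the point, but it does not remove it. The factorial convention suits designs in which every level of the time factor is exposed to treatment; T0 is not. The Bonferroni sentence does not tie the interaction test to the main-effect tests. The promise of confidence intervals does not say that the between-arm change is reported whatever the interaction shows. Nor is this a detail left to a later analysis plan, because the article states the rule itself.

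**Conclusion.** The concern holds in limited form, as a point that should be fixed. The stated rule directs interpretation to a time effect that has no between-arm content and to a group effect that is diluted by one third and carries chance baseline imbalance. As a second route to a group difference, the group effect takes the false-positive rate from 5% to about 10%. At the planned 2.2 μV the fallback is rarely reached, so the harm falls mainly on trials with no effect or a small one.

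The structural point needs no assumption beyond T0 being the baseline recorded before allocation. The percentages rest on the assumed between-patient SDs, on compound symmetry and on reading the pilot figures as changes. The near-certain time effect also needs a shift common to both arms, which the pilot sham figure makes realistic but does not establish. Randomisation, sample size and data collection are unaffected.

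**What to change.** In Data analysis:

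- Delete the clause that sends a non-significant interaction to the main effects.
- Name one confirmatory between-arm contrast for the primary outcome: the difference in change from T0, or the T0-adjusted difference, at one stated post-baseline time. Alternatively, name T1 and T2 together with the Bonferroni correction across the two. Deleting the clause alone is not enough, because it leaves two post-baseline comparisons and no single 5% test.
- Report that contrast with its 95% CI whatever the interaction P value.
- State that time effects, group effects that include T0, and changes within one arm are descriptive and support no treatment claim, for primary and secondary outcomes alike.

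The cost is a wording change, with no extra data or patients. At 32 evaluable per arm a single contrast has power 0.90 with SD 2.7 in both arms and 0.98 with the two stated SDs. If both times are tested at 0.025 (critical value 2.24), power for each contrast is Φ(2.2/(2.7 × √(2/32)) − 2.24) = Φ(1.02) = 0.85 with SD 2.7. With the two stated SDs it is Φ(2.2/√((2.7² + 1.6²)/32) − 2.24) = Φ(1.73) = 0.96. The single contrast is therefore the option that keeps the planned 90% under the plan's conservative SD.

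### The path that decides the primary outcome (interaction test, then Bonferroni-adjusted simple effects or else main effects, with no primary time point) is not the single change contrast on which the trial was sized

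*Protocol article*

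**What the plan says.** **Sample size section.** The quantity chosen for the calculation is "the change in mean amplitude (μV) of the sEMG during the 10-s tonic contraction phase". The pilot inputs are "4.1 ± 2.7 μV in the acupuncture group and 1.9 ± 1.6 μV in the SA group". The result is "32 cases will be required in each group" at alpha 0.05 and 90% power, raised to 38 per group and 76 in total for 15% dropout. The section names no time point and makes no allowance for multiplicity.

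**Data analysis section.** A GEE with group, time and their interaction is fitted to T0, T1 and T2 for primary and secondary outcomes. The interaction is tested first; "if significant, simple effects analyses will be conducted, otherwise main effects will be interpreted". The next sentence is "Multiple comparisons will be adjusted using the Bonferroni correction". All tests are two-sided at 0.05. Only the safety P values are expressly exempt from adjustment.

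**Outcomes section.** There is one primary outcome, mean amplitude in the 10-s tonic phase, recorded at all three time points with none singled out, and there are nine secondary outcomes.

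**The concern.** The sizing describes one comparison: how much more the amplitude changes under acupuncture than under sham. Neither branch of the analysis path delivers that comparison as the deciding test.

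- **Interaction significant.** Simple effects are group differences at a given time or time differences within a group. None of them is a between-group difference in change. They are then Bonferroni-adjusted over a family that is not stated.
- **Interaction not significant.** Main effects are read. The group main effect averages over T0, T1 and T2, so it includes a time point before treatment. It is a second opportunity to find a group difference at 0.05.

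At stake is whether the trial has one fixed criterion for success. As written, a significant interaction, a simple effect at T1, a simple effect at T2 or an overall group effect could each be presented as the primary result, and the overall false-positive rate of the procedure is not 5%.

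**Working it through.** **1. The plan's own figure.** The difference is 4.1 − 1.9 = 2.2 μV. The root-mean-square SD is √((2.7² + 1.6²)/2) = √4.925 = 2.219. By the normal approximation, n per arm = 2(1.960 + 1.282)² × SD²/2.2².

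- Printed SDs: 2 × 10.507 × 4.925/4.84 = 21.4, so 22 (23 by the t or Welch calculation).
- SD 2.7 in both arms: 2 × 10.507 × 7.29/4.84 = 31.7, so 32 (33 by exact t).

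The stated 32 therefore does not follow from the printed SDs. Among the variants tried, it appears only with an SD of 2.7 in both arms, which the protocol does not state. The dropout step does reproduce: 32/0.85 = 37.6, so 38 per arm and 76 in total.

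**2. Does Bonferroni cost the stated power?** Take the sized contrast (difference in change, printed SDs) at 32 evaluable per arm. SE = √((7.29 + 2.56)/32) = 0.555, and the noncentrality is 2.2/0.555 = 3.97. Power at two-sided 0.05/k:

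| k | Level | Power (Welch to normal) |
|---|---|---|
| 1 | 0.05 | 97.3–97.8% |
| 2 | 0.025 | 94.8–95.8% |
| 3 | 0.0167 | 92.7–94.2% |
| 6 | 0.0083 | 88.3–90.8% |
| 9 | 0.0056 | 85.1–88.3% |

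Two comparisons (T1 and T2) or three (each time point) stay above 90%. The line is crossed at about six. The full set of simple effects has 3 group comparisons plus 2 × 3 = 6 within-group time comparisons, which makes 9. With 38 evaluable per arm, k = 9 gives 92.1%.

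**3. False-positive rate of the two-branch path.** Suppose there is no group effect at any time. The interaction is significant with probability 0.05. If it is not, the group main effect is tested at 0.05. Treating the two tests as independent:

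0.05 + 0.95 × 0.05 = 0.0975.

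Simulation gives about 9.8%. Whatever the correlation between time points, the figure cannot exceed 0.05 + 0.05 = 10%.

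**4. What Bonferroni adds after the gate.** The interaction has 2 degrees of freedom. Its null hypothesis is that both change contrasts (T1 − T0 and T2 − T0, between groups) are zero. Once it is rejected, closed testing allows each of these two contrasts to be tested at 0.05. In simulation under no effect, the chance of claiming at least one is about 4.2% without Bonferroni and 3.6% with it. Both are under 5%, and the exact values shift with the assumed correlation. So for these two contrasts the correction only adds conservatism, while the main-effect branch, where the extra error arises, is left as it is.

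**5. What the main effect estimates.** If the true effect were 2.2 μV at both T1 and T2 and zero at T0, the group main effect would be (0 + 2.2 + 2.2)/3 = 1.47 μV. That is not the quantity used for sizing.

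The power of the interaction test itself cannot be computed, because the protocol gives no within-subject correlation and no time-specific effects.

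**The case against.** The strongest reply is that this is a condensed protocol article. It states the model, the order of testing, the adjustment method, sidedness and threshold. Listing the members of a Bonferroni family is commonly left to the analysis plan, and Bonferroni is a valid method. That stands as far as it goes: an unlisted family alone would not be worth raising. It does not answer the point here. The article does fix a decision path for the primary outcome, and that path differs from the comparison the same article used for sizing.

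Three stronger readings are tempting, and the document does not support them.

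- **That Bonferroni takes the trial below 90% power.** On the printed SDs it does not for two or three comparisons. The lower figures (82.9% and 78.5% for two and three) need an SD of 2.7 in both arms, which is not stated. The reserve does come from a sample size that its inputs do not reproduce, but that is a separate matter.
- **That the primary contrast would be judged at 0.0033, over all 15 pairs of the six group-by-time cells.** The text names simple effects, which number at most nine. The other six pairs cross both group and time.
- **That the nine secondary outcomes need a formal cross-outcome correction.** If each were tested at 0.05, the familywise rate would reach 1 − 0.95⁹ = 37% only under independence, and these are overlapping measures from one recording. One primary outcome is named and the trial is presented as mechanistic. Formal control here is a preference.

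**Conclusion.** The concern holds as a mismatch between sizing and analysis. The trial is sized on one between-group difference in change at 0.05. The primary outcome is decided by an interaction test followed by one of two branches, with no primary time point. With no true effect, the chance of a significant interaction or group main effect is about 9.8% against the nominal 5%. This counts either result as a finding for the primary outcome, which the text permits, and assumes the group main effect is tested at 0.05 whenever the interaction is not significant. No loss of the stated 90% power is established. The power figures assume the printed pilot values, 32 evaluable per arm and a change contrast as the test.

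**What to change.** Replace the interaction-then-branch rule for the primary outcome with one contrast estimated from the same GEE: the between-group difference in change from T0 in 10-s tonic mean amplitude, at one post-baseline time point named in advance, tested two-sided at 0.05. Test the same contrast at the other post-baseline time point, also at 0.05, only if the first is significant. This fixed order needs no Bonferroni adjustment. Report the group comparison at T0 and all within-group comparisons descriptively, and do not use a group main effect as a fallback. Label the nine secondary outcomes exploratory. State which time point the pilot changes of 4.1 and 1.9 μV refer to, so that the sized and tested contrasts match.

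The cost is wording only, settled before unblinding, with no added participants and no change to procedures. The one downside is that the second time point can be claimed only after the first, so the choice of the first should rest on the trial's scientific question.
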